**Fig. 4 Fig4:**
[figure not shown]
Screen shot of intervention (green) and control (red) villages in Udalguri: Potential scenarios of intervention-control contamination and subsequent use of geographical buffer to minimize it. Source: Google Maps. **a** Original randomization of baseline survey villages. **b** After discarding villages when intervention and control villages are within 3 KM distance

### Balancing checks

Balance between intervention and control groups was examined with respect to potentially important covariates after randomization of the 240 villages using baseline data. Although randomization happened at the village level, the unit of analysis is the child. Hence, we performed balancing checks at the level of village, child, child’s household and the mother. Balance was re-examined after excluding the villages discarded to minimize intervention-control contamination. Results in Table 3 suggest that reasonably good balance has been achieved across indicators for villages, children, their HHs, and mothers. This is expected as the randomization of villages to intervention and control groups happened within stratum, after stratifying the villages based on several of the indicators presented in Table 3. The two groups remain balanced after excluding intervention and control villages discarded to minimize intervention-control contamination.

**Table 3 Tab3:** Balancing checks based on selected village, household (HH), mother and child-level indicators: comparison between intervention and control groups

Characteristics	After randomization of all 240 baseline survey villages			After discarding villages to minimize contamination (180 villages)		
	Control	Intervention	*p*-value*	Control	Intervention	*p*-value*
Village-level indicators						
Village has subcentre	40.5	39.2	0.8334	39.8	41.7	0.7926
Village has secondary school	31.0	25	0.3034	29.6	26	0.5833
Village experienced flood last year	30.2	37.5	0.2359	31.6	35.4	0.5787
% of HHs in village living more than 50 years in same village	75.9	76.5	0.6841	77.2	76.1	0.8800
% of tribal HHs in village	26.4	26.2	0.5359	25.6	27.3	0.6494
% of mothers in village with education HS ^a^ or more	12.3	13.1	0.6777	12.6	13.6	0.6390
% of mothers in village receiving full antenatal care	41.9	42.1	0.936	42.5	43	0.8386
Household-level indicators						
Average HH size	5.33	5.28	0.4336	5.34	5.3	0.4867
Household head is Muslim	27.9	32.3	0.4104	27.7	30.2	0.6453
Household has (pour) flush toilet	35.9	33.6	0.5033	35.3	35.1	0.9965
Household belongs to poorest wealth quintile	19.7	19.7	0.9838	20.4	17.3	0.2405
Average time (in minutes) from household to vaccination site	19.9	20.6	0.5764	19.9	19.9	0.6037
Mother- and child-level indicators						
Mothers received full ANC when pregnant with child	41.9	41.9	0.9612	42.4	42.9	0.8787
Child was born in health facility	85.9	86.5	0.7941	84.9	88.4	0.2184
Child has vaccination card	92.7	92.4	0.7852	92.1	92.1	0.9731
Child (12–23 month old) is fully immunized	78.5	77.6	0.8244	77.6	77.6	0.8479

*Wilcoxon Rank Sum Test with Null Hypothesis: location parameters of the distribution are the same in each group

^a^*HS* higher secondary

To check balances between intervention and control groups based on selected household, mother and child level characteristics we have adjusted for clustering as responses from HHs (as well as mothers and children) within a village are correlated. However, for checking balance based on village level indicators this adjustment does not have any impact on standard errors and hypothesis testing. All analysis has been done using “survey” package [35] in R [36]. Wilcoxon rank sum test has been adjusted as per the survey design [37].

## Discussion

Pre-specification of study protocol for ongoing studies which includes objectives, rationale and methodology of the study increases confidence in the validity of the conclusions and can reduce publication bias [38].

Our study aims to evaluate the impact of a novel community engagement intervention (SALT) in improving childhood immunization uptake. Our community engagement approach is based on the premise that communities can think and act for themselves, and that communities have the capacity to change themselves. It employs facilitated conversations to elicit community strengths, increase self-awareness and stimulate self-confidence and action. Facilitators accompany the community on its path to ownership of the issue of immunization and its solution.

To identify the impact of SALT in increasing immunization coverage, we adopted an experimental design which is considered to be the gold standard for evaluation studies. Specifically, we used a cluster randomized controlled trial design. To recruit clusters and participants at baseline, we used a two-stage stratified random sampling method. Within a district, first we stratified clusters (villages) based on census data and randomly selected villages from each of the four stratum. At the second-stage, we selected random sub-sample of eligible HHs (having children in the age group of 6–23 months) from each selected village. The baseline survey happened during June–August 2016. Post baseline survey, using baseline data we stratified our sampled clusters again and, within each stratum, we randomly allocated them to the intervention and control groups. Randomization after baseline allowed us to use an extensive set of sociodemographic and economic characteristics for stratification at the village level, which were not available from census data. Moreover, it provided us with a more accurate estimate of ICC and coverage rates leading to re-estimation of appropriately justified sample size.

Note that the rationale to consider *stratification* for sampling design is different from the rationale to consider *stratification* for randomization. While the former ensures a representative sample of villages from Assam, having varied socio-demographic characteristics, the latter guarantees balance between intervention and control groups with respect to potentially important covariates at baseline. Since control group forms the basis for counterfactual theory of causation, it is important to ensure that intervention and control groups are similar and our methodology ensures it. A simple comparison of outcomes between sampled children in villages receiving the intervention and those in control villages would allow us to measure change in vaccination coverage outcomes attributable to SALT. The study uses a repeated cross sectional design. Eligible HHs within a cluster were randomly sampled at baseline and HHs will be sampled again at endline following the same method. An appealing feature of repeated cross sectional surveys is that concerns regarding attrition can be avoided [31]. These features of our evaluation design justify the internal validity of our study.

Cluster randomized controlled trail, by design, minimizes the risk of intervention-control contamination as compared to individual-level randomization where sharing of information is more likely to happen if individuals living within the same cluster receive different interventions [39]. However, cluster randomization design does not guarantee that the threat of contamination will be entirely removed. Contamination of control participants may lead to an underestimation of the intervention effect in the context of improving immunization coverage. This may result in rejection of an effective intervention as ineffective because the observed effect size may neither be statistically significant nor programmatically relevant. Our study attempts to minimize intervention-control contamination through introducing distance buffer between intervention and control villages.

Our community engagement intervention; the SALT approach is participatory, interactive, prolonged and involves multiple inter-related steps. RCTs of complex interventions like SALT are often criticised as being ‘black box’ as it can be difficult to know why and how the intervention worked (or not) [40]. At the end of the study, the absence of an impact could be simply because SALT was ineffective in this particular context or it could potentially be because of less than optimal implementation of the intervention. In order to be able to answer this, we will attempt to ‘unpack’ the ‘black box’ by examining underlying processes. To that end, we developed a process evaluation data collection plan for the entire duration of the intervention phase. Specifically, the aim is to answer the following questions: 1) whether the intervention is implemented as intended, 2) whether the intervention incorporates the primary objective of the study (i.e., increasing immunization coverage), 3) consistency of intervention delivery across communities in terms of the process of administering the intervention, 4) how the intervention was received by the HHs and communities across villages and districts, and 5) whether contextual factors influence the implementation of intervention.

As per our revised sample size (90 villages per group), our study is powered to identify a difference of at least eight percentage points in immunization coverage between the intervention and control groups. Any effect size below that may not be detected and, hence, the intervention may be declared as ineffective. It is true that larger the sample size, higher is the chance of detecting a difference, even one that is smaller than the expected difference. We had to tally these methodological considerations against few practical considerations, which also could affect the quality of evidence.

In order to avoid intervention-control contamination, post randomization we discarded some villages from both groups in case intervention and control villages were located in close proximity. It can be argued that this violates the principle of randomization. However, the process of discarding the villages was done in a blinded manner, without considering the logistics of implementation. We assumed that geographical separation of at least 3 KM between intervention and control villages would reduce chances of interaction of community members between groups. Larger distance buffer would have further reduced the chances; however, enforcing a buffer more than 3KM was not feasible since within a district we could discard only 10 villages from each of the two groups.

Lastly, although stratified sampling was used to ensure that selected districts are representative in terms of socio-demographic diversity of Assam, the districts were purposefully selected so that they were not too far away from the central location Guwahati. We should therefore exercise caution while generalizing the study findings to other parts of the state and the country.

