### Study design

We adopted a cluster randomized controlled trial (cRCT) design with two groups to evaluate the intervention. The intervention group receives SALT intervention for about a year (March 2017–March 2018) along with the routine immunization (RI) services. The control group received RI services alone. Cluster randomized design is appropriate here as opposed to individual or household level randomization as the intervention is intended for implementation at the community (village) level, the village being our unit of randomization.

The study uses a repeated cross sectional design where we track the same sampled villages but draw independent random samples of households (HHs) at baseline and endline. Post intervention, for the endline survey we do not plan to follow up the same HHs unlike most other RCTs, as estimating immunization coverage rates requires targeting a particular age-group of children. The children sampled at baseline would have mostly grown beyond the desirable age limit by the time the endline survey is due. The HHs in the baseline may no longer satisfy the eligibility criteria (having children in that particular age group) at the time of the endline survey – although there may be some overlap.

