### Sample size

To calculate the sample size, we considered the two primary outcomes: DPT3 coverage among 6–23 month old children and FIC among 12–23 month age group. Per our initial (pre-baseline) sample size calculation, we needed 120 villages per group, intervention and control, leading to a total of 240 villages, to detect a difference of at least 10 percentage points in coverage between the two groups, with 80% statistical power using a two-sided test at 5% level of significance, after accounting for the correlation in immunization status among children from the same village. We considered an equal allocation of 240 villages across 3 districts, resulting in 40 intervention and 40 control villages in each of the selected districts. Estimates of the coverage rate for DPT3 and FIC in the control group were obtained from the most recent data available at the time (RSOC, 2013–14) [2]. In Assam, the estimates were 65.9% and 55.3% for DPT3 and FIC, respectively. If the coverage rates for DPT3 and FIC in the intervention group are at least 10 percentage points higher, i.e., 75.9% and 65.3%, respectively, our sample size would allow us to detect the difference in coverage rates between the two groups. To calculate the intracluster correlation (ICC) for these outcomes, we extracted DLHS-3 (2007–08) [28] unit level data for Assam and obtained the estimates as 0.21 and 0.25 for DPT3 and FIC, respectively. We further assumed that a village will have a minimum of 15 children 6–23 month old and 10 children 12–23 month old. If there were more than 15 eligible children in a village, we randomly selected 15 children. Baseline survey was conducted in all 240 villages, as per the requirement of pre-baseline sample size calculation.

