Table 2 presents the revised estimates based on data from baseline survey and the revised sample size. Note that the ICC estimates based on baseline data have decreased relative to earlier estimates from DLHS-3, as anticipated. On the other hand, vaccination coverage rates have increased substantially relative to RSOC data (2013–14). This sudden increase in vaccination coverage can perhaps be attributed to Mission Indradhanush (MI), a flagship program of the Ministry of Health and Family Welfare (MoHFW) and was also observed in other historically poor-performing states such as Bihar, Rajasthan and Madhya Pradesh [30]. Two phases of MI happened before our baseline survey (phase 1: April–July 2015 and phase 2: Nov 2015-Feb 2016) and all three study districts (Bongaigaon, Kamrup rural, and Udalguri) received at least one round of MI intervention. However, it is possible that this high level of immunization coverage will not be sustained in future after the supplementary immunization activities under MI are discontinued. In view of these high coverage rates, we reduced the minimum detectable difference from 10 to 8 percentage points in the revised calculation of sample size.

**Table 2 Tab2:** Revised sample size for two primary outcome variables based on SALT baseline survey (July–August 2016) data

Outcome of interest	Updated coverage rate (%)	Updated ICC	Updated sample size (number of villages in each of intervention and control group)
DPT3	84	0.17	57
FIC	79	0.18	90

Per our revised sample size calculation, we needed 90 villages per group to detect a difference of at least 8 percentage points in coverage between the control and intervention groups with 80% statistical power based on a two-sided test having 5% level of significance, after accounting for the correlation in immunization status among children from the same village. Total number of villages required for the study is 180 (90 × 2). We considered an equal allocation of 180 villages across the 3 districts, resulting in 30 intervention and 30 control villages in each of the three selected districts.

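### The only effect comparison the article names is an unadjusted endline contrast; adjusting for each village's baseline coverage and the 12 randomisation strata could gain precision at no data cost

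*Protocol article*

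**What the plan says.** The article has no analysis section. Its one statement on how the effect is obtained is in the Discussion: "A simple comparison of outcomes between sampled children in villages receiving the intervention and those in control villages would allow us to measure change" attributable to the intervention. Neither baseline coverage nor strata are mentioned there.

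Three other parts of the article bear on this:

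- **Baseline data on the same villages.** Under Study design: "The study uses a repeated cross sectional design where we track the same sampled villages", with fresh household samples at each round. Baseline FIC and DPT3 coverage are therefore already in hand for each village.
- **Stratified allocation.** Under Randomization strategy, villages were allocated within four strata per district, so 4 × 3 = 12 cells. The strata come from a composite score of baseline indicators. The listed indicators cover demography, wealth, maternal education, antenatal care and flooding. Vaccination coverage is not among them.
- **Sample size.** The re-estimation section sizes the trial "with 80% statistical power based on a two-sided test having 5% level of significance", allowing for correlation within villages, and "we reduced the minimum detectable difference from 10 to 8 percentage points in the revised calculation of sample size". Table 2 gives 90 villages per group for FIC and 57 for DPT3.

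**The concern.** With ICCs of 0.17 to 0.18 and 10 to 15 children per village, most of the variance of a village's observed coverage lies between villages. Earlier coverage in the same village can explain part of that component. Because coverage was not used directly in forming the strata, the analysis is the remaining place to use it.

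The strata matter for a related reason. Stratified allocation lowers the true variance of the effect estimate when the strata predict the outcome. An analysis that leaves them out still counts the between-stratum variance as error, so its intervals tend to be conservative.

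What is at stake is power for FIC, the outcome that sets the sample size. The Discussion accepts that an effect below 8 points may be missed and the intervention then declared ineffective.

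**Working it through.** **Inputs.** Table 2: FIC 79%, ICC 0.18, 90 villages per group; DPT3 84%, ICC 0.17, 57 villages per group. Difference 8 points, 80% power, two-sided 5%. Children per village, from the Sample size section: "a minimum of 15 children 6–23 month old and 10 children 12–23 month old". The re-estimation section does not restate these cluster sizes; I assume that they carry over, and the reproduction below supports this.

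**Step 1: reproduce the stated sample size.** Villages per group = (1.96 + 0.8416)² × [p₁(1−p₁) + p₂(1−p₂)] / d² × [1 + (m−1)ICC] / m.

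- FIC: 7.849 × (0.1659 + 0.1131) / 0.0064 = 342.2 children. Design effect 1 + 9 × 0.18 = 2.62. 342.2 × 2.62 / 10 = 89.65. Stated: 90.
- DPT3: 7.849 × (0.1344 + 0.0736) / 0.0064 = 255.1 children. Design effect 1 + 14 × 0.17 = 3.38. 255.1 × 3.38 / 15 = 57.48. Stated: 57.

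Both stated figures come out to the nearest whole village. The pooled-variance formula gives 90.4 and 58.1. The calculation is thus an endline-only comparison with clustering included and no term for baseline coverage or strata.

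**Step 2: how well baseline measures a village.** Reliability of observed village coverage = m × ICC / [1 + (m−1)ICC].

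- FIC: 1.8 / 2.62 = 0.687.
- DPT3: 2.55 / 3.38 = 0.754.

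**Step 3: effect of baseline adjustment.** Let c be the correlation of true village coverage between the two surveys, about two years apart. The article does not give c, so it is an assumption over its whole range. The correlation of observed village coverage is r = c × reliability, and adjustment multiplies the variance by 1 − r². The effective sample per group is then 90m / [design effect × (1 − r²)]; for unadjusted FIC this is 900 / 2.62 = 343.5. Power uses the two-proportion formula with pooled variance under the null.

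FIC, 90 villages per group:

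| c | r | Variance factor | Power at 8 points | Detectable difference (points) |
|---|---|---|---|---|
| 0 | 0 | 1.00 | 79.8% | 8.0 |
| 0.3 | 0.206 | 0.96 | 81.5% | 7.9 |
| 0.5 | 0.344 | 0.88 | 84.6% | 7.6 |
| 0.8 | 0.550 | 0.70 | 91.8% | 6.8 |
| 1 (limit) | 0.687 | 0.53 | 97.1% | 6.0 |

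DPT3 already has room at 90 villages: unadjusted power is 93.7%, with a detectable difference of 6.6 points. That difference falls to about 6.2 at c = 0.5 and 5.4 at c = 0.8.

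**Step 4: why the form of adjustment matters.** A plain difference-in-differences has variance 2(1 − r) relative to the unadjusted endline contrast. For FIC this is 2(1 − 0.344) = 1.31 at c = 0.5 and 2(1 − 0.550) = 0.90 at c = 0.8, against 0.88 and 0.70 for regression on baseline. At c = 0.5 it would be worse than no adjustment.

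**Step 5: strata.** The article does not report how much outcome variance the strata explain, so no figure can be given. The strata and baseline coverage are also likely to overlap in what they explain, so their gains would not simply add.

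**The case against.** The strongest reply is that the Discussion sentence is an argument for internal validity. It says that an unadjusted contrast would suffice, and it does not rule out covariates. The full model may stand in an analysis plan not shown, and its absence from a condensed article is no fault. This stands. A reader might infer that the plan has decided to exclude baseline coverage and strata; the article does not say so. The point rests only on the comparison that the article does name and on a sample size built to match it.

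A reader might also infer that clustering will be ignored, since the article says "Although randomization happened at the village level, the unit of analysis is the child". That sentence introduces the balance checks, which were adjusted for clustering, and both sample size calculations allow for it. Nothing supports a claim of inflated type I error.

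Nor does the article support a claim of bias from baseline imbalance in FIC. Table 3 shows 77.6% in both groups after villages were discarded. For FIC the issue is precision.

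Finally, the gain may be small. The article says that coverage rose suddenly, perhaps through a national campaign, and may not be sustained. Village rankings could therefore shift over two years, and at a correlation of 0.3 or less the FIC variance falls by under 5%. This also stands, and is why the range starts at zero. It does not favour the unadjusted analysis: adjustment for one village-level covariate and the strata costs few of the degrees of freedom from 180 villages.

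**Conclusion.** The point holds as one of efficiency. The comparison named is valid, and with clustering kept it delivers the stated 80% power for FIC at 8 points; no stated figure is wrong. It leaves unused the baseline coverage already collected and the strata already used for allocation. For FIC, which has no power margin, the adjusted analysis is not materially worse at any correlation and is appreciably better if village coverage persists: power is about 85% at an assumed correlation of 0.5 and 92% at 0.8, but only 81.5% at 0.3.

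The figures assume equal cluster sizes of 10 (FIC) and 15 (DPT3), the same ICC at both surveys, and the large-sample variance factor 1 − r². The gain from the strata is not quantified. Confidence is moderate, because the two-year correlation is unknown and an analysis plan not shown may already include these terms.

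**What to change.** Before endline data are seen, name as primary for each primary outcome a child-level model of endline status that accounts for villages (random intercept, or GEE with village as cluster). Adjust it for the 12 district-by-stratum cells and for the village's baseline coverage of the same outcome. Enter baseline coverage as a covariate (ANCOVA form); do not use a plain difference-in-differences. Report the risk difference with its 95% confidence interval, and keep the simple cluster-adjusted comparison as a supportive analysis. If the analysis plan already says this, one sentence in the article pointing to it is enough.

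The cost is some wording and a slightly longer model. No new data and no change to the number of villages are needed.

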### Minimizing intervention-control contamination

In each district, we had randomized the 80 sampled villages to the intervention and control groups in equal proportion. However, according to our revised sample size calculation, we needed only 30 intervention and 30 control villages, that is, we had the liberty to exclude 10 villages from each of the two groups. We attempted to use this opportunity to minimize intervention-control contamination while excluding villages, as opposed to random exclusion.

Transfer of knowledge is a crucial component of SALT intervention. Particularly, during the knowledge fair, the community may have an opportunity to meet peers from the control community and share their knowledge and experience, in case intervention and control villages are located in close proximity. To mitigate potential contamination between intervention and control villages, we attempted to ensure that the intervention and control villages are sufficiently far apart from one another. For our community-based intervention, by separating the intervention and control villages geographically we seek to reduce the chances of interaction between community members belonging to the intervention and control groups. The following procedure was used to ensure geographical buffer between intervention and control villages.

After randomization, we plotted the intervention and control villages on Google Maps by uploading an excel file of villages having locations (defined by “village name, district name, state name”) as a column. Different-color place marks were used for intervention and control villages. Using features of Google Maps, we then calculated straight line distances between intervention and control villages when they visibly appeared to be close by. If the distance is less than 3 km (KM), we discarded one of the villages. While discarding villages, we were mindful about two things: 1) an equal number of intervention and control villages are being discarded and 2) distribution of intervention and control villages across strata does not change significantly as that might have an impact on balance between the two groups.

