Figure 4 illustrates the procedure using two Google Maps screenshots. In Panel a, we plot all 80 villages from Udalguri district that were randomized to intervention (green) and control (red) groups and in Panel b we present the same plot after discarding villages in instances where intervention and control villages are within 3 KM distance. For example, in bottom left corner, two control villages appeared to be located in close proximity to three intervention villages. Distance calculation confirmed that the straight line distance is less than 3 KM and, hence, two control villages were discarded (circled in blue in Panel a and b). Using the same rationale, two intervention villages were also discarded as seen in the top left and top middle part of the plot (circled in blue in Panel a and b).

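### Discarding of villages after randomization is called blinded, but the methods show the arm was visible, so selection among the 180 retained villages cannot be ruled out

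*Protocol article*

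**What the plan says.** All 240 baseline villages were randomized, 40 per arm in each of three districts. The revised sample size needed only 30 per arm per district, so 10 per arm per district could be dropped. The section on minimizing contamination says this freedom was used to "minimize intervention-control contamination while excluding villages, as opposed to random exclusion".

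The procedure in that section runs as follows:
- "After randomization, we plotted the intervention and control villages on Google Maps".
- "Different-color place marks were used for intervention and control villages".
- Straight-line distances were calculated for pairs that looked close on the screen.
- "If the distance is less than 3 km (KM), we discarded one of the villages".
- Two considerations guided the choice. One was that "an equal number of intervention and control villages are being discarded". The other was that the spread across strata should not change much.

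In the worked example from Udalguri, "two control villages appeared to be located in close proximity to three intervention villages", and the two control villages were dropped. Two intervention villages were dropped elsewhere in the same district.

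The Discussion concedes that this step can be said to violate randomization, and replies that "the process of discarding the villages was done in a blinded manner, without considering the logistics of implementation". The section on balancing checks concludes from Table 3 that "The two groups remain balanced after excluding intervention and control villages discarded to minimize intervention-control contamination". The Discussion also holds that a simple comparison of outcomes between arms would measure the change attributable to the intervention.

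**The concern.** Randomization makes the two sets of 120 villages comparable in expectation. It does not do so for a subset picked afterwards by people who can see the arm and choose which village of a pair to lose. Blinding of that choice would be a real safeguard, and the article offers it as its answer to the objection. If the choice was not blind, that answer fails. The causal reading of an unadjusted comparison then depends on an undocumented selection step. The statement would also probably be carried into the results paper.

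**Working it through.** **1. The statement against the procedure.** The Discussion says the discarding was blinded. The contamination section says it came after allocation, on a map coloured by arm. Keeping discards equal per arm also requires knowing each village's arm. Finding mixed pairs needs only the knowledge that two villages differ in arm, so the choice within a pair could have been made by a fixed rule or at random with labels hidden. No such rule is stated. The only content attached to the word blinded is that implementation logistics were not considered, which is a different matter from allocation.

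**2. How many were dropped.** Table 2 gives full immunization coverage (FIC) of 79%, ICC 0.18 and 90 villages per arm. The difference is 8 points, with 80% power at two-sided 5%. The sample size section assumes 10 children aged 12–23 months per village.
- Children per arm = (1.960 + 0.842)² × (0.79×0.21 + 0.87×0.13) / 0.08² = 342.2.
- Design effect = 1 + 9 × 0.18 = 2.62.
- Villages = 342.2 × 2.62 / 10 = 89.6, so 90. The plan's figure is reproduced, and 120 − 90 = 30 were discarded per arm.

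**3. Absolute gap between arms in Table 3, before → after discarding.**

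| Widened | | Narrowed | |
|---|---|---|---|
| Poorest quintile | 0.0 → 3.1 | Flood last year | 7.3 → 3.8 |
| Facility birth | 0.6 → 3.5 | Secondary school | 6.0 → 3.6 |
| Tribal households | 0.2 → 1.7 | Muslim head | 4.4 → 2.5 |
| Subcentre | 1.3 → 1.9 | Flush toilet | 2.3 → 0.2 |
| Over 50 years in village | 0.6 → 1.1 | FIC, 12–23 months | 0.9 → 0.0 |
| Full antenatal care (village) | 0.2 → 0.5 | Travel time (minutes) | 0.7 → 0.0 |
| Full antenatal care (mother) | 0.0 → 0.5 | Vaccination card | 0.3 → 0.0 |
| Higher secondary education | 0.8 → 1.0 | Household size (persons) | 0.05 → 0.04 |

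Eight widened and eight narrowed.

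**4. Implied make-up of the discarded villages.** With equal weight per village, the discarded mean is (120 × before − 90 × after) / 30, with rounding error of about ±0.35 points.
- Poorest quintile: control (120×19.7 − 90×20.4)/30 = 17.6%; intervention (120×19.7 − 90×17.3)/30 = 26.9%.
- Facility birth: control (120×85.9 − 90×84.9)/30 = 88.9%; intervention (120×86.5 − 90×88.4)/30 = 80.8%.
- FIC: control (120×78.5 − 90×77.6)/30 = 81.2%; intervention 77.6%.

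**5. Could this be chance?** A rough standard error comes from the p-values after discarding, scaled by √(90/30).
- Poorest quintile: p = 0.2405 gives |z| = 1.174, so SE = 3.1/1.174 = 2.64, scaled to 4.57. Then 9.3/4.57 = 2.03, p about 0.04.
- Facility birth: SE = 3.5/1.231 = 2.84, scaled to 4.93. Then 8.1/4.93 = 1.64, p about 0.10.
- Flood, the next largest: p about 0.13.

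As a cross-check, take 30 × 15 = 450 children per arm and variance [p₁(1−p₁) + p₂(1−p₂)]/450 × (1 + 14 × ICC). An assumed ICC of 0.05 to 0.30 gives p from about 0.01 to 0.14 for poorest quintile and 0.009 to 0.13 for facility birth. None of these is adjusted for looking at 16 indicators.

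**6. Denominators.** The yes/no village percentages do not fit 120 and 90 if unweighted: 40.5% of 120 is 48.6 villages. Counts that would fit are 126 to 98 for control and 120 to 96 for intervention. With those, step 4 gives 17.2% vs 29.3% for poorest quintile and 89.4% vs 78.9% for facility birth. The direction is the same, but these counts are stated nowhere.

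**7. Possible effect on the estimate.** Assume, since the article gives no figure, that FIC differs by 10 to 30 points between poorest and other households. A 3.1-point gap then shifts FIC by 3.1 × 0.10 = 0.3 to 3.1 × 0.30 = 0.9 points, against a design difference of 8.

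**The case against.** The article hides nothing about the procedure. It reports the coloured markers, the screening by eye and the non-random exclusion, and it raises the randomization objection itself. The sentence can be read as meaning blind to logistics only. The choice was also constrained by a 3 km trigger, equal discards per arm and attention to strata. Geometry may have settled some cases, as when removing two control villages resolves closeness to three intervention villages.

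Most of that stands, and it limits the charge to an incorrect word and an undocumented choice. It does not rescue the word. Being blind to logistics does not answer the objection about randomization, and the constraints leave open which village of a pair went.

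A reader might go further and infer from Table 3 that opposite kinds of villages were removed from the two arms, or that the effect is biased towards the intervention. The documents do not support that. Table 3 does not list the discarded villages, gaps narrowed as often as they widened, and baseline balance on FIC improved to equality. Intervention villages also remain the more flood-affected (35.4% vs 31.6%).

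Covariate adjustment is commonly left to the analysis plan, which is not at hand, so its absence here is no fault. Choosing wealth and facility birth because they moved is data-driven, which is why they belong in a sensitivity analysis only.

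**Conclusion.** The concern holds in a limited form. The discarding was not blind to allocation, on the article's own description. This needs no assumption beyond the ordinary meaning of blinded in reply to an objection about randomization. Selection among the 180 retained villages therefore cannot be ruled out, and the non-significant p-values in Table 3 do not settle it.

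Its size is uncertain and may be small. The visible shifts are 0.0 to 3.1 points for poorest quintile and 0.6 to 3.5 points for facility birth. Chance is a plausible explanation for both. The contrasts between discarded villages in the two arms rest on equal village weights and on 120 and 90 villages per arm. The illustrative shift of 0.3 to 0.9 points in FIC rests on an assumed wealth gradient and covers that one imbalance only.

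**What to change.** In the Discussion, delete the claim of blinding. State that the arm was visible when villages were discarded, who chose the village in each close pair, and by what rule, or that there was none. List the step as a limitation of the causal claim.

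Before the endline survey, pre-specify an estimate adjusted for village baseline coverage (FIC or DPT3) and the randomization strata, to be reported beside the simple comparison. Add a sensitivity analysis that also adjusts for wealth and facility birth. If the analysis plan already contains such an estimate, a reference to it is enough.

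The cost is a text correction and a few covariates from baseline data already collected in all 240 villages. The downside is that a stated strength becomes a stated limitation.
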